##### Urine albumin-to-protein ratio (uAPR)

As a rough estimate of glomerular vs. tubular injury). In the Aim 1 cross-sectional arm, we will obtain one uAPR from all HIV-positive ART-treated adults (including the 500 newly enrolled HIV-positive adults [on ART < 24 months] plus the 2000 ART-experienced PWH who we call back from the R3 Study.

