#### Study outcomes

Prevalence and extent of albuminuria (uACR > 30 mg/g), hypertension (e.g., elevated blood pressure, Stage 1 hypertension, and Stage 2 hypertension), sickle cell trait and disease, hepatitis B & C infection, and Cytomegalovirus (CMV) infection, all stratified by HIV status.Prevalence of *APOL1* variants (high-risk (2 copies of *APOL1* risk variants) and low-risk (0–1 copies of *APOL1* risk variants), by HIV status.Proportion of ART-treated adults with suspected tubular albuminuria (urine albumin-to-protein ratio (uAPR) < 40%) [24, 25] as identified during Aim 1 cross-sectional evaluation.Proportion of ART-treated adults with suspected glomerular albuminuria (albumin-to-protein ratio (uAPR) ≥ 40%) [24, 25] as identified during Aim 1 cross-sectional evaluation

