Procedure / Visit (month (mo))	Enrollment	6 mo	12 mo	24 mo	30 mo
Seated blood pressure check	X	X	X	X	X
Diabetes mellitus screening (perform fasting blood glucose if any signs/symptoms suggestive of underlying diabetes)	X^*^	X	X	X	X
uACR^a^ (No urine protein testing necessary for enrolled Aim 2 HIV-positive adults with normoalbuminuria as all HIV-positive ART-treated adults from Aim 1 will have one uAPR measurement) (We will have stored urine at 3 timepoints to go back and perform uAPR testing in patients with incident microalbuminuria)	X^#^ (We will use Aim 1 uACR as participants baseline value)		X		X
Serum creatinine (SCr)^b^	X (We will use Aim 1 SCr as their baseline value)		X		X
Parasite screening					
Complete blood count (CBC) with differential^c^	X	X	X	X	X
Urine dipstick (spun for all patients with hematuria followed by urine microscopy (*S. haematobium*)	X	X	X	X	X
Malaria testing (rapid diagnostic test) at point-of-care (POC) using fingerprick specimen	X	X	X	X	X
Filariasis POC testing for *Wuchereria bancrofti*^d^	X				X
Onchocerciasis testing (bilateral skin snips)^e^	X				X
Stool for ova and parasite (stool O&P)^f^	X	X	X	X	X
Daytime thick blood smear for *Loa loa* (10 AM–2 PM)	X				X
Strongyloides IgG serology (plasma)^g^	X				X
Tuberculosis screening^h^	X	X	X	X	X
Inflammatory biomarkers (urine and plasma)^i^	X				X
CD4 cell count	X				X
Viral load (plasma HIV RNA)	X				X
Social and Behavioral data	X		X		X
Additional tubes for storage^j^	X		X		X

*All potentially eligible Aim 2 participants will undergo fasting blood glucose testing to evaluate for diabetes (and if ≥ 6.1

mmol/L (110 mg/dL), then patient may have diabetes, is ineligible, and is referred to medical provider/clinic for evaluation

^#^All participants will use their recent uACR measurement (obtained in Aim 1) for their baseline

^a^Two 3 mL sterile universal containers taken for uACR testing (Urine protein testing only for HIV-positives)

^b^Two 3 mL gold top tubes taken to measure serum creatinine (SCr)

^c^CBC with differential—looking for eosinophilia (common with Filariasis (especially *Loa loa*) and Schistosomiasis)

^d^POC testing for *W. bancrofti* antigen by Filariasis Test Strip (FTS), followed by obtaining nocturnal thick blood smears for

microfilaria [between 10 pm—2 am] in FTS-positive persons. *Brugia spp. *are not endemic to Africa, so testing for *W*

*bancrofti* will be sufficient

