^e^*Onchocerca volvulus *ELISA is not sensitive enough to rule out infection. Physical exam findings are also not sensitive. No one

will want to be snipped every 6 months, but since filarial worms are long-lived (> 5 years), snipping at the beginning and end

of study should capture anyone who is infected at study onset or becomes infected during the study

^f^Stool for O&P to be done screening for *S. mansoni* and soil transmitted helminths (e.g., Ascaris, Trichuris, Hookworm)

^g^Strongyloides IgG ELISA at baseline in ALL participants & test all persons testing NEG at enrolment again at 30 months

^h^Sputum specimens (5 mL) to be collected and sent for Gene Xpert testing and/or microscopy (acid fast bacilli staining)

^i^Two 3 mL purple top tubes for plasma biomarkers and one 5–7 mL urine specimens for urine biomarkers (and stored)

^j^Two 3 mL purple top EDTA tubes and one 5–7 mL urine specimen to be obtained and stored for future/approved testing

*Clinical Assessments* at all comprehensive study visits will be performed by trained study nurses and will include:*Vital signs:* temperature, respiratory rate, heart rate, blood pressure (Seated BP checked every study visit using a validated Omron series 5 upper arm digital BP device).*Anthropometrics*: height, weight, waist circumference*Urine albumin testing*, *uACR measurements*: Albuminuria will be assessed at each visit and categorized as defined in Aim 1. Subjects with incident macroalbuminuria will be referred to a clinician for evaluation and to a nephrologist for additional testing/management, per standard of care.*Urine albumin-to-protein [uAPR] ratios (HIV-positive participants)*: will be assessed to screen for possible TDF-mediated tubular insult as a contributing cause of microalbuminuria. Subjects with *uAPR* < *40%* will be classified as *tubular albuminuria* and those with *uAPR* ≥ *40%* will be classified as *glomerular albuminuria*.*Diabetes screening*: All potentially eligible Aim 2 participants will undergo fasting/random blood glucose testing to evaluate for diabetes (and if ≥ 6.1 mmol/L (110 mg/dL), then patient may have diabetes, is ineligible, and is referred to medical provider/clinic for evaluation. Once enrolled, during each study visit, participants will be screened for symptoms of diabetes. In those with symptoms, we will perform fasting/random blood glucose testing. if ≥ 6.1 mmol/L (110 mg/dL), they will be immediately referred to a specialist for further evaluation.

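### A single 40% uAPR cut-off, applied whatever the uACR, lets the tubular/glomerular label depend on the level of albuminuria, so low-grade albuminuria can be called tubular without tubular injury

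*Protocol article*

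**What the plan says.** The protocol article uses uAPR in three places.

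- **Aim 1, Study measures and Study outcomes.** In Aim 1, "we will obtain one uAPR from all HIV-positive ART-treated adults", described as "As a rough estimate of glomerular vs. tubular injury". One study outcome is "Proportion of ART-treated adults with suspected tubular albuminuria (urine albumin-to-protein ratio (uAPR) < 40"%), and a companion outcome counts suspected glomerular albuminuria at 40% or more. Neither outcome is limited by uACR.
- **Aim 2, Study measures (Clinical Assessments).** In HIV-positive participants the ratio "will be assessed to screen for possible TDF-mediated tubular insult as a contributing cause of microalbuminuria". The rule is "uAPR* < *40%* will be classified as *tubular albuminuria" on one side and "uAPR* ≥ *40%* will be classified as *glomerular albuminuria" on the other.
- **Aim 2, Table 6, uACR row.** Stored urine is kept "to go back and perform uAPR testing in patients with incident microalbuminuria".

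The rule has no minimum uACR or total protein, no stratification by uACR and no indeterminate class.

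**The concern.** uAPR is albumin divided by albumin plus everything else. Tubular injury raises the non-albumin part. A low ratio, however, can come from a large non-albumin part or from a small albumin part. A person with healthy tubules and constant background protein can be tubular at a uACR just above 30 mg/g and become glomerular later only because albumin excretion has risen.

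Two results are at stake. The Aim 1 proportions with suspected tubular and glomerular albuminuria could partly reflect how mild the albuminuria is rather than where it comes from. In Aim 2, every participant enters below 30 mg/g, so many incident cases will lie only a little above that line, where the ratio is most easily pulled under 40%. The screen is there to look for an effect of TDF, and urine protein is measured only in HIV-positive participants. A sizeable tubular share could therefore be taken for a drug effect, with no HIV-negative comparison to show otherwise.

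**Working it through.** **Inputs from the protocol article**
- Cut-off: uAPR 40% (Aim 1 Study outcomes; Aim 2 Study measures).
- Microalbuminuria: uACR 30 to 300 mg/g (Aim 2 Study outcomes).
- uACR in people with HIV: mean log10 1.35, SD 0.554 (Aim 1 Sample size).
- Albuminuria prevalence in R3: about 40% (Background).

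**Assumed input:** background non-albumin protein *n*, in mg per g creatinine, in a person without tubular injury. The article gives no value, so a range is shown.

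**Step 1. Check the stated distribution.** Median = 10^1.35 = 22.4 mg/g, as stated. P(uACR > 30) = 1 − Φ((1.477 − 1.35)/0.554) = 1 − Φ(0.229) = 40.9%, in line with about 40%. The normal model on the log10 scale is usable.

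**Step 2. Rewrite the rule.** With albumin A and non-albumin protein N, both per g creatinine:

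A/(A + N) < 0.40 ⇔ 0.6 A < 0.4 N ⇔ N > 1.5 A ⇔ A < N/1.5.

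| uACR (mg/g) | N needed for a tubular label (mg/g) |
|---|---|
| 30 | > 45 |
| 50 | > 75 |
| 100 | > 150 |
| 200 | > 300 |
| 300 | > 450 |

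The requirement rises tenfold across the study's own microalbuminuria range. This holds whatever *n* is.

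**Step 3. Share mislabelled among those with uACR > 30.** If everyone has healthy tubules and background *n*, the share is P(30 < uACR < n/1.5) / P(uACR > 30), with P(uACR ≤ 30) = 0.5907 and P(uACR > 30) = 0.4093.

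| n (mg/g) | n/1.5 | P(uACR < n/1.5) | Share called tubular |
|---|---|---|---|
| 45 or less | 30 or less | – | 0% |
| 60 | 40.0 | 0.6754 | 0.0847/0.4093 = 21% |
| 80 | 53.3 | 0.7519 | 0.1612/0.4093 = 39% |
| 100 | 66.7 | 0.8038 | 0.2131/0.4093 = 52% |

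Letting *n* vary between people (lognormal, log10 SD 0.2, assumed) gives 16% at a median of 50 mg/g and 31% at 70. Within uACR 30 to 100 the shares are 23% and 44%; above 100 they are about 1% or less. The error is concentrated at low uACR.

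**Step 4. Aim 2 incident cases.** Simulation: the mean of two readings is below 30 mg/g at entry and a later single reading is above 30. Within-person log10 SD is 0.15 to 0.30, with no true change or with random drift of log10 SD 0.2; all of these are assumptions. The median first positive uACR is about 37 to 48 mg/g. The share called tubular with healthy tubules is 0% at n = 45 (exact, since every case exceeds 30), 13–29% at 50, 34–65% at 60 and 59–91% at 80.

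**The case against.** The other side has several good points.

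- **Range.** A reader might infer that the ratio fails throughout microalbuminuria. It does not. Above n/1.5, background protein alone cannot bring it under 40%, and if *n* is 45 mg/g or less nobody above 30 mg/g is mislabelled this way. This stands and limits the point to the lower part of the range.
- **Unknown background.** *n* is not in the article, and the two references cited for the cut-off are not at hand, so the size cannot be settled. This stands. What does not depend on *n* is that the amount of non-albumin protein demanded changes with uACR.
- **Hypothesis (c).** A reader might also infer that the test of cumulative TDF exposure is biased. The Aim 2 Statistical analysis plan models time to albuminuria and repeated log10 uACR; uAPR enters neither, nor is it among the Aim 2 outcomes. That test is untouched.
- **Hedged wording and other markers.** The measure is called rough, suspected and a screen, and Aim 2 plans NGAL and KIM-1. The hedges admit imprecision but not an error that moves in one direction with uACR. NGAL and KIM-1 are not part of the classification and are planned only in Aim 2, so they do not help the Aim 1 outcomes. This answers the objection only in part.

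**Conclusion.** The point holds in a limited form. A fixed 40% cut without regard to uACR ties the label to albuminuria level: in the lower microalbuminuria range, below n/1.5, normal background protein can give a tubular label, and with heavier albuminuria true tubular injury can be called glomerular. It affects the two descriptive Aim 1 uAPR outcomes and the Aim 2 uAPR screen of incident cases, and nothing else.

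The size rests on the assumed *n* and on the stated uACR distribution: 0% to 52% of participants above 30 mg/g for *n* up to 100 mg/g. For Aim 2 incident cases it also starts at 0% and then climbs faster, with figures that depend further on the assumed within-person variation. The documents do not support saying that the ratio is useless across 30 to 300 mg/g, or that the study's inference on TDF rests on it. The change is worth making because it is cheap and the affected proportions are named outcomes.

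**What to change.** 1. Among participants with uACR > 30 mg/g, report the uAPR classes by uACR level, not as one overall proportion.
2. Add non-albumin protein-to-creatinine (urine protein/creatinine minus uACR, same sample) as a continuous measure, and relate it to cumulative TDF exposure with adjustment for uACR.
3. Do not read uAPR below 40% at low uACR as tubular unless that measure, or the planned NGAL and KIM-1 in Aim 2, supports it. Otherwise call the case indeterminate.
4. If a cut-off for non-albumin protein is taken from the study's own normoalbuminuric people with HIV, derive it from, or check it in, those with little or no TDF exposure. The Background says that most R3 participants had received TDF at some point, so an unselected reference could absorb the effect being looked for.

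Cost: wording and analysis only, since albumin, protein and creatinine assays are already planned. Some low-grade cases will become indeterminate, and the difference between two assays run by different methods is noisier when protein is low.

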#### Co-infection screening

*Mycobacterium tuberculosis* (TB): Sputum specimens for acid fast bacilli (AFB) microscopy and/or Gene Xpert testing in patients having a cough of ≥ 2 weeks in duration, weight loss, and/or night sweats). Mycobacterial blood cultures, lymph node aspirates, body fluid (i.e., thoracentesis) and imaging studies will be obtained per standard of care when evaluating for suspected extrapulmonary TB.*Parasitic infections* (see Table 6) (The results obtained from enrollment filariasis (*W. bancrofti, O. volvulus, and L. loa*) screening will determine the need for repeat testing at the 30-month visit (i.e., if prevalence is extremely low, we will not re-test at the 30-month visit).

#### *Adverse clinical outcomes* will be assessed at all study visits by trained study research staff

*Hospitalizations:* We will ask all participants if they have been hospitalized in the previous 6 months. If they answer affirmatively, we will ask the reason for hospitalization and approximate dates.*Death*: Ascertained from medical records or from a contact identified by the participant during consent.*Inflammation* will be assessed from plasma and urine specimens collected, as detailed in Table 6. Plasma inflammatory biomarker assay testing will be performed in duplicate at the DMPI Biomarker Core Facility using the Mesoscale Discovery Platform. Based on the literature, we chose a panel of plasma and urine biomarkers [92–101] that will help us elucidate the processed by which chronic inflammation contributes to albuminuria. Urine inflammatory/tubular injury biomarker assay testing will be performed at the [name] laboratory (Brigham and Women’s Hospital Biomarker Laboratory, Boston, MA, USA). Some are novel biomarkers whose role in clinical research is being defined.*Plasma inflammatory markers:* highly sensitive C-reactive protein (hsCRP), IL-6, soluble TNF-receptor 1 (TNFR-1), soluble TNF-receptor 2 (TNFR-2), IL-1β, and TNF (with biomarker levels of sCD14, fibrinogen, and possibly additional plasma biomarker levels to be ascertained pending additional funding/approved sub-studies).*Urine inflammatory/tubular injury biomarkers*: NGAL, KIM-1, and MCP-1 (with biomarker levels of IL-18, interferon-gamma inducible protein-10 (IP-10), and possibly additional urine biomarker levels to be ascertained pending additional funding/approved sub-studies).

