#### Study procedures

Whole blood and urine biospecimens will be obtained for processing for plasma and urine pellets which will be processed and shipped to their respective research laboratories, namely, Duke University (plasma biomarker, *Cytomegalovirus* (CMV) IgG antibody (Ab) testing, and *APOL1* genotyping) and Brigham and Women’s Hospital (urine biomarkers and urine albumin, creatinine, and protein testing). Participants will receive reimbursement for comprehensive study visits. All HIV-negative study participants will be asked to complete a brief risk assessment at each study visit, with reflex viral load testing in those deemed high risk, as outlined in Aim 1 (study procedures). If their HIV test results are positive, they will no longer participate in longitudinal follow-up. Data collected prior to seroconversion will be maintained. Longitudinal assessments (enrollment visit and then every 6 months for 30 months for a total of 5 scheduled visits for each participant) will include the following (*as outlined below*):

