### Statistical considerations

#### Sample size

We will enroll 1500 (1000 HIV-positive and 500 HIV-negative) patients with normoalbuminuria and follow them for up to 30 months. Table 7 summarizes differences in albuminuria incidence that we will have 80% power to detect between the HIV-positive and HIV-negative groups, over a range of sample sizes and albuminuria incidence rates in the HIV-positive group. We will have approximately 80% power to detect a difference of developing albuminuria of 10% (HIV-positive) vs. 5.9% (HIV-negative), or a relative risk of about 1.70 (Bold emphasis row in Table 7).

**Table 7 Tab7:** Detectable alternative for various rates of developing albuminuria for the HIV-positive adult patients

HIV-positive adults, N	HIV-negative adults, N	3-year incidence of albuminuria for HIV-positive adults	3-year incidence of albuminuria, HIV-negative adults, 80% power to detect	Relative Risk
1000	500	5%	2.2%	2.28
**1000**	**500**	**10%**	**5.9%**	**1.70**
1000	500	15%	10.0%	1.51

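### The 6-month hospitalization question covers all of Aim 2 follow-up only if there is a month-18 visit; Table 6 has none, and the text and table on the visit schedule disagree

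*Protocol article*

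**What the plan says.** Three places in the Specific aim 2 part of the protocol article bear on this.

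- **Adverse clinical outcomes.** These "will be assessed at all study visits by trained study research staff". For hospitalizations: "We will ask all participants if they have been hospitalized in the previous 6 months". Participants who say yes are then asked for the reason and approximate dates. For death, a separate source is named: "Ascertained from medical records or from a contact identified by the participant during consent".
- **Study procedures.** Longitudinal assessments are described as "enrollment visit and then every 6 months for 30 months for a total of 5 scheduled visits for each participant".
- **Study measures, Table 6.** The column heads are "Procedure / Visit (month (mo)) Enrollment 6 mo 12 mo 24 mo 30 mo". No procedure has a month-18 entry.

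The Study measures section also lists items taken from the medical record and self-report and updated at each scheduled visit. Dates of comorbid diagnoses are on that list; hospital admissions are not.

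**The concern.** The look-back has a fixed length and is not tied to the previous visit. It therefore assumes that consecutive visits are never more than 6 months apart, and Table 6 has a 12-month interval between months 12 and 24. Under that table, a participant admitted at month 14 can truthfully answer no at every visit, and the record cannot tell an unasked period from one without admissions.

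At stake is the completeness of an adverse clinical outcome that the study sets out to collect, with reasons and dates. Any later count of admissions over 30 months would be too low, and the loss would be hard to recover because the question was not put at the time.

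**Working it through.** **Inputs.** Look-back of 6 months (Adverse clinical outcomes). Visits as in the Study procedures text or as in Table 6. Follow-up of 30 months and 1500 participants (Aim 2 Sample size: "We will enroll 1500 (1000 HIV-positive and 500 HIV-negative) patients with normoalbuminuria and follow them for up to 30 months").

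**Step 1: the stated visit count.** Enrollment plus a visit every 6 months to month 30 gives 0, 6, 12, 18, 24 and 30, which is six visits, not five. Five can be reached in two ways:
- counting only visits after enrollment: 6, 12, 18, 24, 30;
- using the Table 6 columns: enrollment, 6, 12, 24, 30.

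The sentence names the enrollment visit before giving the total, which fits the second count better. Its stated interval fits only the first. The text does not settle the matter.

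**Step 2: months covered.** A visit at month v covers the interval from v − 6 to v. Coverage is the union of these intervals over the follow-up visits.

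| Schedule | Intervals asked about | Covered | Not covered |
|---|---|---|---|
| Table 6 (6, 12, 24, 30) | 0–6, 6–12, 18–24, 24–30 | 24 of 30 | 12–18 |
| 6-monthly (6, 12, 18, 24, 30) | 0–6, 6–12, 12–18, 18–24, 24–30 | 30 of 30 | none |
| Table 6, asked since last visit | 0–6, 6–12, 12–24, 24–30 | 30 of 30 | none |

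**Step 3: size under Table 6.** 6/30 = 20% of follow-up. With full follow-up of everyone, that is 1500 × 6 = 9,000 of 1500 × 30 = 45,000 person-months.

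**Step 4: what share is missed.** The document gives no admission rate, so this step rests on an assumption of a constant rate r per month.
- Admissions (all events): expected number missed is 6r of 30r, or 20% whatever r is.
- Participants ever hospitalized: the true share is 1 − exp(−30r) and the detected share is 1 − exp(−24r). As r becomes small the shortfall approaches 1 − 24/30 = 20%. With an illustrative r = 0.02, the shares are 1 − exp(−0.60) = 45.1% and 1 − exp(−0.48) = 38.1%, a shortfall of 1 − 38.1/45.1 = 15.5%. It is below 20% because some participants with an admission in months 12–18 are picked up through another one.

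**Step 5: missed visits.** Under Table 6, missing the month-6 or month-12 visit leaves 12 of 30 months (40%) unasked. Any fixed recall window loses time in this way, so this is not a separate contradiction, but the same change of wording removes it when a later visit is attended.

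**The case against.** The strongest reply is that the gap is conditional. The Study procedures text puts visits at 6-month intervals, which includes month 18, and then coverage is complete. The 6-month question fits that schedule, and Table 6 footnote e, which explains why skin snips are not repeated at each interval, also assumes 6-monthly visits. On this reading the fault is a missing column in Table 6, and it would affect blood pressure, blood count, stool, malaria and tuberculosis screening as well. This stands: a reader might infer that admissions in months 12 to 18 are certain to be lost, and the document does not establish that. It contains two incompatible schedules, and only one of them produces the gap.

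A second reply concerns importance. Hospitalization is not among the Aim 2 study outcomes, and it does not appear in the sample size or statistical analysis sections. This also stands. A reader might infer a biased comparison of admissions by HIV status, or a biased planned rate. The document describes neither analysis, and a gap in the schedule falls on both HIV groups alike.

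A third reply is that diagnosis dates, updated at every scheduled visit, could reveal a serious illness in the unasked period. That is possible, but admissions are not on the abstraction list, so it is incidental capture and not a stated route.

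None of this removes the need to act: the question as worded is safe only under a schedule that Table 6 contradicts.

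**Conclusion.** The point holds in conditional form. The fixed 6-month question and the Table 6 schedule do not fit together, and the Study procedures text, which would make them fit, gives a visit total that agrees with Table 6 once enrollment is counted.

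If Table 6 governs, 20% of follow-up is never asked about. About 20% of admissions would then go unrecorded, and up to 20% of ever-hospitalized participants, less where admissions recur. These shares assume a constant admission rate, full attendance and no incidental capture from records. If a month-18 visit takes place, there is no scheduled gap.

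The consequence is under-counting of a collected adverse outcome. The albuminuria and kidney-function outcomes and the power figures do not change. It is worth correcting because the correction is nearly free and the data cannot be fully recovered later.

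**What to change.** 1. Reconcile the Aim 2 Study procedures text with Table 6: state whether a month-18 visit exists, and make the interval, the visit total and the table columns agree.
2. In the Adverse clinical outcomes section, ask at each follow-up visit about hospitalization since the last completed study visit, with that visit's date pre-filled in REDCap. Keep the 6-month look-back at enrollment only, where it records history.

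The second change closes the gap under either schedule, and it also covers time before a late visit or after a missed one, provided the participant attends again. It costs one sentence and one case report form prompt, with no added visit or specimen. The drawback is that recall over 12 months, as at month 24 under Table 6, is less exact than over 6. Both changes are best made before follow-up data are collected.
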